#### Outcome assessments

All outcome assessments will be evaluated by well-trained investigators who are blind to the treatment/groups allocation. Moreover, another researcher will perform independent random cross tests. Assessments will be performed at baseline (1 month prior to treatment) and after 1 month, 3 months, and 6 months’ follow-up.

#### Primary outcome measures

The Western Ontario and McMaster Universities Osteoarthritis Index (WOMAC) is a widely-used scale in the assessment of OA. The successful application of WOMAC has proven its validity, reliability, and responsiveness in OA patients. Researchers have conducted a number of empirical studies have been conducted to estimate the MCID and PASS of the WOMAC in patients with OA. A 10-point numeric rating scale of WOMAC will be the primary outcome [46]. The WOMAC score will be normalized to a 100-point scale. In bilateral OA cases, when both knees meet the eligibility criteria, one of them will be treated and the WOMAC index will evaluate the same knee through the study period.

#### Secondary outcome measures

The secondary outcome measures are cartilage thickness measurement, visual analog scale (0 to 100 mm) for pain (VAS), a quality-of-life index (QLI), range of knee motion, muscle strength, global posture analysis system (GPS), and Likert scale. Moreover, the researcher will document safety records, including adverse events and serious adverse events, in addition to interventions and/or co-interventions, such as exercise, yoga, medication, and self-applied massage. Moreover, clinical examinations will be undertaken at the same intervals to document joint line tenderness warmth, effusions, erythema, and limitation in range of motion.

#### Magnetic resonance imaging (MRI)

As Previous studies have shown that tibial-plateau bone area associates with the development of osteoarthritis [47]. A three Tesla-MRI with volumetric 3D gradient and fast spin echo sequences will be performed. Osiris software (Digital Imaging Unit, University Hospital of Geneva, Switzerland) will be used in Image processing. The volume of the cartilage plates (femoral condyles, tibial plateaus and patellar) will be manually isolated from the total volume. Data will be resampled using bi-linear and cubic interpolation for the 3D interpretation, while Osteophytes, will not be involved in the area of interest.

The cartilage plate volume will be calculated by adding values of the pertinent voxels within the resultant binary volume. Moreover, Semi-quantitative measures of cartilage defects will be obtained using a modified International Cartilage Repair Society (ICRS) score as it demonstrated in Table 2.

**Table 2 Tab2:** modified International Cartilage Repair Society (ICRS) score scale

Modified International Cartilage Repair Society (ICRS) score	
Grade 0	Normal cartilage
Grade 1	Focal blistering and intra-cartilaginous low- signal intensity area with an intact surface and bottom
Grade 2	Irregularities on the surface or bottom and loss of thickness of less than 50%
Grade 3	Deep ulceration with loss of thickness of more than 50%
Grade 4	Full-thickness cartilage wear with exposure of subchondral bone

### Sample size calculation

The current study was designed to achieve 80% power overall to detect a 10-point change on the WOMAC between groups after 6 months (the significance level was set at 0.05). Based on an earlier study using a similar outcome measuring method with adding around 20% for the overall attrition rate. Thus a sample size of 96 (32 per group) will be used for estimating a two-sided 95% confidence interval (CI) [48].

The statistical hypotheses are:

H0: mean WOMAC Index (with LIPUS) = mean WOMAC Index (conventional).

HA: mean WOMAC Index (with LIPUS) ≠ mean WOMAC Index (conventional).

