### Mesenchymal stem cells (MSCs) derivation

we will conduct the isolation and expansion procedure by following the method designed by Zuk et al. [38] The aspirated content in the filter will be treated in a fully sterile environment in a Biological Safety Cabinet (Class II) and obeying strict aseptic systems with (ISO 5) air quality at least. Moreover, all the equipment, reagents, and buffer will be sterile, validated, and qualified for cell culture use. Stromal vascular fraction (SVF) will be isolated by enzymatic digestion followed by centrifugation.

Later, cell culturing will be accomplished under hypoxic conditions and using a standard growth medium (10% fetal bovine serum). The cells will be cultured to reach a confluency of about 80% and later passage 2 (P2). Upon reaching P2, the researcher will wash the cells to remove the fetal bovine serum. Then, HADMSCs will be suspended in a clinical-grade MSC cryoprotectant media and cryo-preserved by a clinical-grade cryoprotectant media [39, 40].

The cells will be detected via flow cytometry (FACS), which will be completed independently on all HADMSC samples using the four surface markers for the MSCs, as indicated by the International Society for Cellular Therapy (ISCT) [41]. The researcher will also test the presence of MSC markers (CD44, CD 90, CD105, and CD 73) and the absence of hematopoietic surface markers (CD 34 and CD45). In addition, all HADMSC samples will undergo independent sterility testing for microbial growth or/and contamination.

Dosages including roughly 10* 10^6^ MSCs each will be frozen separately in sterile cryovials in an approved cell cryoprotectant medium using a validated control rate freezing method and kept in liquid nitrogen until needed [40]. On the day of injection, one cryovial will be liquefied at 37 °C using a sterile water bath and then centrifuged to eliminate the cryoprotectant medium and add injectable sterile isotonic (0.9%) normal saline to a total of 3 ml. Cell count and viability will be established through the use of a Muse Cell Analyzer (Merck Millipore, USA).

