### Statistical analyses

Data will be recorded in the case report form. The outcomes will be presented as the mean ± standard deviation (SD). Data analysis will be done using the SPSS version 24.0 statistical software. Comparing the outcomes between groups will be calculated using analysis of variance (ANOVA) or an alternative nonparametric test if the conditions for parametric tests are not applicable.

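### ANOVA is the only stated method for a four-visit outcome with about 20% expected loss; in either usual form it drops incomplete cases, which a mixed model would avoid

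*Protocol article*

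**What the plan says.** Three parts of the protocol article bear on this point.

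- **Sample size calculation.** The trial is sized for "80% power overall to detect a 10-point change on the WOMAC between groups after 6 months". The basis for the number and the allowance for loss are given as "Based on an earlier study using a similar outcome measuring method with adding around 20% for the overall attrition rate", and the section concludes that "a sample size of 96 (32 per group) will be used".
- **Outcome assessments.** All outcomes, WOMAC included, are assessed at baseline and at 1, 3 and 6 months.
- **Statistical analyses.** The one method given is "Comparing the outcomes between groups will be calculated using analysis of variance (ANOVA"), with a nonparametric test as the alternative if parametric conditions fail.

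The article does not say whether the ANOVA is one-way at a single visit or repeated-measures. It also does not say how the 1- and 3-month scores enter the 6-month comparison.

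**The concern.** The named method fits this design poorly on either ordinary reading. A one-way ANOVA, or its rank-based counterpart, of 6-month scores leaves out each patient without a 6-month value, however many earlier scores that patient gave. A classical repeated-measures ANOVA does use the earlier visits, but it needs complete rows and so leaves out anyone with one visit missing.

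The 20% inflation protects power. It does not protect the comparison if the patients who leave differ from those who stay and do so differently by arm. At stake is whether the 6-month contrast still reflects the randomised groups, together with some precision that the planned visits would supply at no extra cost.

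**Working it through.** **Inputs from the article:** 10 WOMAC points at 6 months, 80% power, two-sided 5%, 32 per arm, about 20% loss, follow-up at 1, 3 and 6 months.

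**Assumed, because the article does not give them:** the WOMAC SD, the correlation between visits (0.6), the loss rate in each arm, and how loss relates to outcome.

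**Expected loss.** 96 × 0.20 = 19.2 patients. 32 × 0.80 = 25.6 remain per arm, or 76.8 in total.

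**The plan's own figure.** The SD is not stated, so 96 cannot be reproduced forward, but it can be solved back. For a pairwise comparison, n per arm = 2(1.96 + 0.84)² SD² / 10².
- SD 12.5 gives 25, and 25 / 0.8 = 31.25, rounded up to 32.
- SD 12.76 gives 26, and 26 × 1.2 = 31.2, rounded up to 32.

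So 32 per arm is consistent with an SD of about 12.5 to 12.9. The value 12.5 is used below.

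**Bias by formula.** In one arm, the completer mean differs from the full mean by (loss fraction) × (mean gap between completers and dropouts). If the gap is the same in both arms, the bias in the contrast is (difference in loss rates) × (gap). For an assumed gap of 10 points:
- 20%/20%: 0 × 10 = 0
- 15%/25%: 0.10 × 10 = 1.0
- 10%/30%: 0.20 × 10 = 2.0
- 5%/35%: 0.30 × 10 = 3.0

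With no gap, the bias is 0 at any split.

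**Bias by simulation.** Two arms of 32, true difference 0, SD 12.5, correlation 0.6, 4,000 runs per row. All patients have 1- and 3-month scores, and only the 6-month score can be missing. Where loss is linked to outcome, the chance of leaving rises with the 3-month score. The estimate using earlier visits is a regression of the 6-month score on arm and the 1- and 3-month scores, averaged over all patients. It is a simple stand-in for the mixed model and does not use baseline.

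| Loss in the two arms | Linked to 3-month score | Bias, 6-month completers | Type I error, completers | Bias using earlier visits |
|---|---|---|---|---|
| 20% / 20% | no | 0.0 | 5.1% | 0.0 |
| 20% / 20% | yes | 0.0 | 5.0% | 0.0 |
| 10% / 30% | no | -0.1 | 4.8% | -0.1 |
| 10% / 30% | yes | 1.3 | 6.3% | 0.1 |
| 5% / 35% | no | 0.0 | 4.7% | 0.0 |
| 5% / 35% | yes | 1.8 | 8.3% | 0.0 |

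The two approaches agree. The simulated biases correspond to a completer-dropout gap of about 6 points (1.3 / 0.20 = 6.5; 1.8 / 0.30 = 6.0).

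**Precision.** At 20%/20% unrelated loss, the SD of the estimated difference is 3.52 for completers only and 3.38 using the earlier visits. The variance ratio is 3.38² / 3.52² = 0.92, a gain of about 8%.

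**The case against.** The strongest reply is that this is a condensed article. Analysis sets, missing-data rules and sensitivity analyses commonly sit in a full protocol or SAP that is not shown, and inflating the sample for attrition is ordinary practice. That stands. The attrition sentence is not an error, and silence on those rules is not part of this point. What remains is that the article does name a method for the comparison, and a better one exists for the data it plans to collect.

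Some stronger readings are tempting but lack support.

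- **The plan deliberately analyses completers only and discards the early visits.** A reader might infer this, but the article does not say so. The exclusion follows from how the usual forms of ANOVA work.
- **Losses will differ by arm.** The ultrasound burden does not show this, because session length and frequency are the same in all three groups. Nor does cell-product failure. The article says "all HADMSC samples will undergo independent sterility testing for microbial growth or/and contamination", but a failed product affects treatment, and nothing says such patients leave assessment. Groups 1 and 2 both need cells, so it cannot separate them; at most it separates either of them from the saline group. The Blinding section says participants cannot be blinded, so expectation-driven loss is possible, but no rates by arm are given.
- **Unequal loss by itself biases the result.** It does not, as the rows with loss unrelated to outcome show.
- **Error rates of 9% or 13%.** These arise if one arm loses 20% who would have scored 10 or 15 points worse (bias 0.20 × 10 = 2 or 0.20 × 15 = 3 points) while the other loses patients at random. That one-sided pattern, like the SD, is an assumption and not a forecast from the article.

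It is also fair to say that the simulation favours the longitudinal approach, because it ties loss to a score that is always observed.

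**Conclusion.** The point holds as a weakness in the choice of method. With about 19 of 96 patients expected to be lost, either usual form of ANOVA excludes incomplete cases and gives up some precision (about 8% of variance in the one setting simulated). It can also bias the 6-month contrast, but only if loss is related to outcome and differs between arms.

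Under the assumed SD of 12.5, correlation of 0.6, and loss of 10%/30% to 5%/35% linked to the 3-month score, the bias is about 1 to 2 points, or 13% to 18% of the 10-point target. Type I error is then about 6% to 8% instead of 5%. With balanced loss of the same kind in both arms, or loss unrelated to outcome, the bias is about zero. The article does not show which situation will arise, so the bias is possible and not established.

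**What to change.** In the Statistical analyses section, replace ANOVA for the primary outcome with a mixed model for repeated measures:

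- WOMAC at 1, 3 and 6 months as the response, in all randomised patients by assigned arm;
- arm, visit, arm-by-visit interaction and baseline WOMAC as fixed effects;
- unstructured covariance across visits;
- the between-arm contrast at 6 months as the primary comparison.

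The cost is a change of wording and slightly more analysis work. No extra patients, visits or measurements are needed, and the planned software can fit the model. There are two limits. The model corrects only loss that can be predicted from observed data, and it recovers nothing for a patient with no score after baseline.

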S.R.Angle /2011	Rat	Ultrasound have a positive effect on osteogenic differentiation of rat bone marrow stromal cells.	27
Ji Hao Cui/2007	Mouse	Ultrasound could be an effective cue to upregulate chondrogenic differentiation of MSCs .	28
Jiang, T /2012	In vitro	LIPUS may induce the osteogenic differentiation of ADSCs in vitro.	29
Jang /2014	In vitro	LIPUS might be used to promote cartilage healing by inducing the migration of CPCs to injured sites.	30
Yamaguchi /2016	Rat	MSC injection with LIPUS is more effective than either treatment in promoting concurrent cartilage repair .	32

*MSC* Mesenchymal stem cells, *ADSC* Adipose stem cells, *CPC* Chondrogenic progenitor cell

Zhou et al. demonstrated that, in addition to accelerating and augmenting the osteogenic differentiation of stem cells, the combination of LIPUS and MSC implantation could prolong the preservation of MSC in vitro [31]. Likewise, Yamaguchi et al. revealed that the combination of the intra-articular injection of MSC and LIPUS showed better results in improving cartilage repair and subchondral reformation in vivo than single treatment [32].

In the present study design, we developed a randomized controlled trial to evaluate the MSC and LIPUS combination among patients with knee osteoarthritis. We hypothesized that the combination of HADMSCs and LIPUS would promote the effectiveness of MSCs in knee cartilage regeneration more than a single-treatment approach.

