**Fig. 1 Fig1:**
[figure not shown]
Study flowchart

Treatment groups will receive different treatment regimens as follows:
❖ Group 1: Single intra-articular injection of 10* 10^6^ HADMSCs with low-intensity pulsed ultrasound treatment for 20 min daily, 5 days a week, for up to 8 weeks.❖ Group 2: Single intra-articular injection of 10* 10^6^ HADMSCs with shame ultrasound irradiation for 20 min daily, 5 days a week, for up to 8 weeks.❖ Group 3: Normal saline with low-intensity pulsed ultrasound treatment for 20 min daily, 5 days a week, for up to 8 weeks.

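### The printed hypothesis matches neither the three arms nor the stated aim, and the three-group ANOVA tests a third question, so the primary comparison is not identified

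*Protocol article*

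**What the plan says.** **Arms** (Protocol article, Study design, treatment list). Group 1 receives stem cells plus LIPUS. Group 2 receives stem cells plus sham ultrasound. The third is "Group 3: Normal saline with low-intensity pulsed ultrasound treatment for 20 min daily".

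**Aim** (Background). "We hypothesized that the combination of HADMSCs and LIPUS would promote the effectiveness of MSCs in knee cartilage regeneration more than a single-treatment approach". The Discussion repeats this as the combination against the individual approaches.

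**Formal hypotheses** (Sample size calculation). "H0: mean WOMAC Index (with LIPUS) = mean WOMAC Index (conventional"), with the two-sided alternative "HA: mean WOMAC Index (with LIPUS) ≠ mean WOMAC Index (conventional"). The same section gives "80% power overall to detect a 10-point change on the WOMAC between groups after 6 months", and "the significance level was set at 0.05".

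**Test** (Statistical analyses). "Comparing the outcomes between groups will be calculated using analysis of variance (ANOVA"), or a nonparametric alternative if the parametric conditions fail.

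**The concern.** The article contains three different statements of what is being tested.

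- The aim needs two contrasts: Group 1 versus Group 2 (does LIPUS add to cells?) and Group 1 versus Group 3 (do cells add to LIPUS?).
- The printed null is a single two-group statement whose two labels cannot be mapped to the arms. Two arms are *with LIPUS*, and none is *conventional*.
- The ANOVA null is that all three means are equal.

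What is at stake is how the main result is interpreted. A significant F says that some arm differs from another. It may do so only because the arm without cells does worse, which says nothing about whether LIPUS improves stem-cell therapy. The 80% power claim has the same problem, because it is not attached to any named pair of arms.

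**Working it through.** **Inputs.** From Sample size calculation: 10 WOMAC points, two-sided 0.05, 80% power, about 20% attrition, 32 per group (96 in total). Evaluable per arm: 32 × 0.8 = 25.6, taken as 26. The SD is not printed; the section says only "Based on an earlier study using a similar outcome measuring method". It is therefore an assumption, and a range is shown.

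**The plan's own figure.** Without an SD, 96 cannot be reproduced. It can be solved backwards from n per arm = 2(1.96 + 0.842)² SD² / 10² = 0.157 × SD².

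- SD 12.6: 24.9, so 25 per arm; 25 / 0.8 = 31.25, so 32; 3 × 32 = 96.
- SD 12.8: 25.7, so 26 per arm; 26 × 1.2 = 31.2, so 32; again 96.

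So 96 fits one unadjusted two-group comparison with SD near 12.6 to 12.9. It also fits an omnibus ANOVA with 26 per arm: 80% power is reached at SD 13.15 for means (0, 10, 10) and at SD 11.4 for (0, 5, 10). The total does not reveal which test was sized. SD 12.62 is used below because it gives 80% power for one pair with 26 per arm.

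**Scenario A: LIPUS adds nothing to cells.** Mean improvements are 10, 10 and 0 in Groups 1, 2 and 3.

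- Grand mean 6.67; squared deviations 11.1 + 11.1 + 44.4 = 66.7.
- Noncentrality λ = 26 × 66.7 / 12.62² = 10.9, with 2 and 75 degrees of freedom.
- P(F significant at 0.05) = 0.833.
- Group 1 versus Group 2 has a true difference of 0 and rejects 5% of the time. By simulation, F is significant while 1 versus 2 is not in about 78% of trials (83% less the 5% in which both are significant).

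| Assumed SD | Omnibus F significant |
|---|---|
| 10 | 96% |
| 12.6 | 83% |
| 15 | 68% |
| 20 | 43% |

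**Scenario B: cells add nothing to LIPUS.** Group 1 equals Group 3, and Group 2 is 10 points worse. At SD 12.8 the omnibus F is again significant 82% of the time. Group 1 versus Group 2 alone rejects about 79% of the time, although the combination is no better than LIPUS alone. So a test of 1 versus 2 cannot carry the aim by itself either.

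**Scenario C: the combination beats both single arms by 10.** Group 1 versus Group 2 alone has about 80% power at SD 12.62. The two contrasts share Group 1, so their joint power was simulated. Both are significant in about 69% of trials, falling to 51% at SD 15 and 27% at SD 20.

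**The case against.** **The natural reading is Group 1 versus Group 2.** The Abstract describes the question as the effect of LIPUS on stem-cell therapy, and 32 per arm fits a single pairwise comparison. On that reading the null is sensible. This is fair as a guess at the intent. But the article does not say so, Group 3 also receives LIPUS, and combination versus LIPUS alone, half of the aim, still falls outside the hypothesis.

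**Contrasts belong in an analysis plan that is not shown.** Their order, the alpha allocation and the role of the earlier visits may well be there, and their absence here is no fault. The point rests only on the printed hypotheses, which disagree with the printed arms and aim. An analysis plan naming 1 versus 2 and 1 versus 3 would be replacing this hypothesis, not elaborating it.

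Three stronger readings are tempting and are not supported:

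- *The trial will be declared positive when LIPUS adds nothing.* No section makes a significant F the success rule. In Scenario A, F and Group 1 versus Group 2 are both significant in only about 5% of trials. The 83% shows that F is uninformative about LIPUS, not that a false claim follows.
- *Error is uncontrolled if unadjusted pairs follow the ANOVA.* With exactly three groups, pairs tested only after a significant F hold the family-wise error at about 5% under the global null.
- *LIPUS will be pooled across Groups 1 and 3.* Nobody plans this; it is one literal reading of the null. On it, Scenario A gives a true difference of 5 points against LIPUS, with SE = 12.62 × √(1/52 + 1/26) = 3.03. It rejects about 37% of the time in the direction of harm. Power in Scenario C is also about 37%.

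**Conclusion.** Wrong as written. The printed null and alternative do not fit the design or the aim, and the ANOVA matches neither. This follows from the text and needs no assumption.

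The size of the consequence does depend on assumptions: 26 evaluable per arm, a common SD, a 10-point deficit in the saline plus LIPUS arm, and an SD the article does not give. Over SD 10 to 20 the probability of a significant F that reflects only the missing cells runs from 96% down to 43%. The qualitative conclusion does not change over that range.

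**What to change.** Replace the null and alternative in Sample size calculation with two named contrasts on the normalised (0–100) WOMAC at 6 months: Group 1 versus Group 2, and Group 1 versus Group 3. Pre-state a rule that controls alpha. One example is 1 versus 2 first at two-sided 0.05, then 1 versus 3 at two-sided 0.05 only if the first is significant; the order is the sponsor's choice. Claim superiority to both single treatments only if both contrasts succeed. Report each difference with its 95% confidence interval. In Statistical analyses, make the omnibus test secondary.

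State the SD and tie the 80% power to the named contrast it describes.

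**Cost.** The rewording needs no extra patients or data, but it has a price to disclose. With 96 randomised, 80% power applies to Group 1 versus Group 2 alone, and power to win both is about 69% under the same assumptions. If the sponsor wants 80% for both, then at SD 12.8 about 32 evaluable per arm are needed: 32 / 0.8 = 40 randomised per arm, or 120 in total.

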### Statistical analyses

Data will be recorded in the case report form. The outcomes will be presented as the mean ± standard deviation (SD). Data analysis will be done using the SPSS version 24.0 statistical software. Comparing the outcomes between groups will be calculated using analysis of variance (ANOVA) or an alternative nonparametric test if the conditions for parametric tests are not applicable.

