### Inclusion criteria

Males and females aged 18 to 70 Years old.Radiological diagnosis of osteoarthritis using the American College of Rheumatology criteria.Radiological grading of Grade II–III osteoarthritis (OA) of the knee as determined by a qualified radiologist using the Kellgren and Lawrence system.Medial or lateral compartment OA .Less than 5 degrees varus or valgus knee deformity as measured by the long mechanical axis of the knee on x-ray.A minimum pain score of equal or greater than 5/10 on a visual analogue scale (VAS)

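### The stated ANOVA makes no use of baseline WOMAC and may give way to a rank test; a prespecified baseline-adjusted ANCOVA would gain power at no cost

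*Protocol article*

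**What the plan says.** The Statistical analyses section of the protocol article gives this rule: "Comparing the outcomes between groups will be calculated using analysis of variance (ANOVA) or an alternative nonparametric test if the conditions for parametric tests are" inapplicable. One rule covers all outcomes, and no other section gives a separate rule for the primary outcome. It names no covariate, no criterion for the switch and no substitute test.

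On the primary outcome, the Primary outcome measures section says "The WOMAC score will be normalized to a 100-point scale". On timing, the Outcome assessments section says "Assessments will be performed at baseline (1 month prior to treatment) and after 1 month, 3 months, and 6 months’ follow-up". A pre-treatment value is therefore planned for each participant.

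The Sample size calculation section claims "80% power overall to detect a 10-point change on the WOMAC between groups after 6 months", at a significance level of 0.05, with 32 per group after an allowance of about 20% for attrition. Its null and alternative hypotheses are written on the mean WOMAC Index, not on ranks and not on change scores.

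**The concern.** Two features of the stated rule cost something.

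- **Unused baseline.** A plain ANOVA of the 6-month score leaves in the error term all the between-patient variation that the baseline score could explain. With arms this small, a chance baseline difference also carries into the 6-month contrast in proportion to the correlation between the two measurements.
- **The switch.** If the parametric conditions are judged to fail, the primary comparison becomes a rank test. That no longer addresses the stated hypothesis on means, and it does not itself yield an estimate on the scale of the 10-point target. Which question the primary test answers then depends on the data.

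What is at stake is power and clarity of the primary result. The validity of the test is not in doubt.

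**Working it through.** **Inputs from the article:** difference 10 points; power 80%; significance level 0.05 with a two-sided interval; 32 per group; attrition about 20%.

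**Assumed, because the article gives neither:** the SD of WOMAC, and the correlation r between baseline and 6-month WOMAC (0.3 to 0.6).

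**Step 1: evaluable patients.** 32 × 0.80 = 25.6, so about 26 per arm.

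**Step 2: the plan's own figure.** Without an SD, the sample size cannot be reproduced forwards. Solved backwards, a pairwise two-sample t test with 26 per arm has 80% power for 10 points when the SD is 12.62. The unadjusted 80% below is therefore true by construction.

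**Step 3: power under three analyses.** With equal SDs at both times:

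- ANCOVA residual SD = SD × √(1 − r²). At r = 0.5: 12.62 × √0.75 = 10.93.
- Change-score SD = SD × √(2(1 − r)). At r = 0.5: 12.62 × √1 = 12.62.

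Pairwise t-test power for 10 points, 26 per arm, SD 12.62:

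| r | ANOVA of 6-month score | ANOVA of change | ANCOVA |
|---|---|---|---|
| 0.3 | 80.0% | 65.8% | 83.6% |
| 0.5 | 80.0% | 80.0% | 89.9% |
| 0.6 | 80.0% | 88.0% | 93.8% |

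If the SD were 15 (also an assumption), ANOVA of the 6-month score would have 65.4% power, and ANCOVA 69.5%, 77.7% and 83.8% at the same three correlations.

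In sample-size terms, the gain at r = 0.5 is 1/(1 − 0.25) = 1.33, equivalent to one third more patients.

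**Step 4: chance imbalance.** The standard error of a baseline difference between two arms is 12.62 × √(2/26) = 3.5 points. A gap of 4 points or more in either direction therefore arises in about 25% of pairwise comparisons. Given a 4-point gap and r = 0.5, the unadjusted 6-month contrast is off by about 0.5 × 4 = 2 points. This error is conditional on the observed gap and averages to zero over randomisations.

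**Step 5: the switch.** The article does not define the conditions, so a plausible version was simulated with three arms of 26: go to Kruskal-Wallis if any Shapiro-Wilk test or the Levene test gives p < 0.05.

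| Data | Sent to rank test | Type I error of two-stage rule | ANOVA and rank test disagree (10-point shift in one arm) |
|---|---|---|---|
| Normal | about 18% | 5.1% | about 5% |
| Skewed (gamma) | about 97% | 5.1% | about 9% |

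**The case against.** The strongest reply is that this is a condensed article. Covariates, assumption checks and the name of the rank test normally belong in the full protocol or analysis plan, so their absence is no fault. For the unnamed fallback test and the undefined conditions, that largely stands. It does not cover the whole point, because the article does name a method and a conditional switch, and a better method is available from data already being collected.

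A second reply is that the sample-size wording about a 10-point change may mean change scores, in which case baseline is used. The hypotheses on the mean WOMAC Index point the other way without settling it. Either way, ANCOVA has the higher power at every correlation examined. The gap narrows as r rises: at r = 0.7 it is 95.1% against 97.5%.

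Third, the size of the gain rests on assumed values. That stands. The VAS entry threshold may narrow the baseline range and lower r, and at r = 0.3 the gain is under 4 percentage points.

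A reader might also infer three stronger claims that the documents do not support:

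- **That the test would be chosen unblinded.** No section says so. The Blinding section says only that investigators receive unblinded data after the study is complete.
- **That the unadjusted comparison is biased.** Randomisation keeps it unbiased on average.
- **That the switch inflates the false-positive rate.** In the simulation it stayed near 5%.

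**Conclusion.** The point holds as one of efficiency and prespecification. The stated ANOVA is valid but gives up power that the baseline measurement would supply: about 4, 10 or 14 percentage points at r = 0.3, 0.5 or 0.6, given an SD of about 12.6 and 26 evaluable per arm. Both r and the SD are assumptions, and the loss vanishes only as r approaches zero. Adjustment would also remove the effect of chance baseline imbalance from the estimate. The switch matters less for error rates than for meaning, since it would exchange the stated hypothesis on means for a comparison of ranks on the primary outcome. This is a free improvement.

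**What to change.** In the Statistical analyses section, state that the primary analysis is ANCOVA of 6-month normalised WOMAC on treatment arm and baseline WOMAC, reported as adjusted mean differences with 95% CIs. Keep a rank-based test as a sensitivity analysis only.

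Use the same baseline-adjusted model for the continuous secondary outcomes: VAS, range of motion, muscle strength, and cartilage thickness or volume. Keep ordinal methods for the ICRS grade (0 to 4) and the Likert scale, where a linear model of means is a poor fit. Adding Kellgren-Lawrence grade as a covariate (the inclusion criteria admit "Radiological grading of Grade II–III osteoarthritis (OA) of the knee") and using robust standard errors are optional.

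The cost is one paragraph. No new data are needed, and the planned software can fit the model.
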